#### Health facility surveys

All 21 selected health facilities will be surveyed. See Table 3 for facility details.

#### Key informant interviews

This component will include individuals 18 years of age or older who are either implementing partners or intervention health facility staff. Implementing partners are defined as IH programmatic staff members employed in the catchment area of interest. Health facility staff are defined as clinical or administrative MoH employees working at one of the 21 health centers. Approximately 42 key informants from the 21 health facilities (21 implementing partners and 21 clinical health facility staff) will be included.

### Sample size determination

This study is powered to detect a change by cluster in under-five mortality per 1000 live births. A sample size of 7600 participants will provide 80% power to detect an estimated 30% reduction or greater of under-five mortality from the estimated baseline of 70 per 1000 live births, with an alpha of 0.05, intracluster correlation of 0.005, 20% non-response rate, and estimated 0.5 children under five per participant [9, 55]. Effect size is a conservative estimate based on past pilot experience (ClinicalTrials.gov Identifier: NCT03773913).

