#### Stepped-wedge cluster randomized control trial

This pragmatic design leverages the sequential or staggered rollout of the ICBHSS model and will facilitate an assessment of effectiveness as well as implementation strategy through coverage and adoption metrics by comparing geographically organized clusters [50, 51]. It includes four clusters that organize intervention health facilities by district: Bassar, Binah, Dankpen, and Kéran. The ICBHSS cluster initiation order will be randomized annually with four steps, as it was independently determined by the IH programs team that baseline health needs were similar in each cluster. Community-based household surveys adapted from Demographic and Health Survey (DHS) modules previously implemented in Togo [3] and focusing on demographic, maternal, and child health data will be conducted in each cluster at baseline, 12, 24, 36, and 48 months.

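### The 7600 participants are given without a unit; read as the study total, as the sentence stands, they give about 26–30% power in the stated stepped wedge, not 80%

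*Protocol article*

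**What the plan says.** The section on sample size determination introduces the figure as the power of the study, for a change by cluster, and gives one number: "A sample size of 7600 participants will provide 80% power to detect an estimated 30% reduction or greater of under-five mortality". The starting risk is put at 70 per 1000 and the significance level at 0.05. The remaining inputs are "intracluster correlation of 0.005, 20% non-response rate, and estimated 0.5 children under five per participant". No formula is named. The text does not say whether the test is one- or two-sided, or whether the intracluster correlation applies to districts or facilities.

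The design section describes the layout to which the number must apply. On clusters: "It includes four clusters that organize intervention health facilities by district". There are four steps, with one district starting each year. Household surveys "will be conducted in each cluster at baseline, 12, 24, 36, and 48 months", which makes five rounds. Under the inclusion criteria for the household survey, households are drawn afresh each year and one eligible woman per household is interviewed. The design is therefore a repeated cross-section with 4 × 5 = 20 district-by-round cells.

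**The concern.** A single unqualified sample size in a section on the power of the study is most naturally read as the total. The article supplies no multiplier for rounds or districts. Yet the five rounds each take a new sample, so 7600 could be the total, one fifth of it (per round) or one quarter of it (per district).

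Under-five mortality is the primary effectiveness outcome and is meant to inform national policy. If 7600 is the total, a true 30% reduction would be missed roughly seven times in ten, and a null result could be misread as absence of effect. If it is per round, the field effort is five times the printed figure. A reader cannot tell which study is planned.

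**Working it through.** **Inputs from the article.** Risks 0.070 and 0.070 × 0.7 = 0.049, so the difference is d = 0.021; alpha 0.05; ICC ρ = 0.005; 20% non-response; 0.5 children per participant; I = 4 districts; T = 5 rounds; one district crossing over per step.

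**Assumptions not in the article.** Two-sided test, equal district sizes, a cluster effect constant over time, and a binary risk per child. The individual variance σ² is taken as the baseline value 0.070 × 0.930 = 0.0651, or as the average of the two arms, (0.0651 + 0.0466)/2 = 0.05585. Ranges below run from the first to the second.

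**Formula.** Hussey–Hughes model with fixed period effects and m children per cell: s² = σ²(1 − ρ)/m and τ² = σ²ρ.

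Var = I·s²(s² + Tτ²) / [(IU − W)s² + (U² + ITU − TW − IV)τ²]

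For this layout U = 10, W = 0 + 1 + 4 + 9 + 16 = 30 and V = 16 + 9 + 4 + 1 = 30. So IU − W = 10 and U² + ITU − TW − IV = 100 + 200 − 150 − 120 = 30. Power = Φ(d/√Var − 1.96).

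**Step 1: can the plan's figure be reproduced?** Yes, per survey round. Solving for 80% power gives 743 children per cell with the baseline variance, that is 743 × 4/0.4 ≈ 7,434 women per round, within 3% of 7600. With the average variance it gives about 6,344 per round. Over five rounds these come to about 37,200 and 31,700 women. No two-sided variant tried reproduces 7600 as a study total.

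**Step 2: study total, without clustering.** 7600 × 0.8 × 0.5 = 3,040 children. An individual 1:1 comparison needs (1.960 + 0.842)² × (0.0651 + 0.0466)/0.021² ≈ 1,988 per group, or 3,976 children. With 1,520 per group, z = 0.021/√(0.1117/1520) = 2.45 and power = Φ(2.45 − 1.96) = 68.8%. Counting deaths agrees: a hazard ratio of 0.70 needs 247, and 3,040 × 0.0595 ≈ 181 are expected. So 80% is out of reach before the stated ICC or the period effects enter.

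**Step 3: study total, stated stepped wedge.** m = 3,040/20 = 152. With the baseline variance:
- s² = 0.0651 × 0.995/152 = 0.000426 and τ² = 0.0003255
- Var = 4 × 0.000426 × (0.000426 + 0.0016275)/(0.00426 + 0.009765) = 0.0002496, so SE = 0.0158
- z = 1.33 and power = 26%

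With the average variance SE = 0.0146, z = 1.44 and power = 30%. If the 21 facilities (5, 7, 4 and 5 per district) are the clusters, power is 30–35%. With four districts and ICC set to 0 it is 36–41%.

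The reduction detectable with 80% power for four districts is about 54–55% with the average variance recomputed at that effect. With the baseline variance it is larger: 2.80 × 0.0158 = 0.0443, or 63%.

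**Step 4: all readings, four districts, ICC 0.005.**

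| 7600 means | Children per cell | Women sampled in all | Power |
|---|---|---|---|
| Study total | 152 | 7,600 | 26–30% |
| Per district, all rounds | 7600 × 0.4/5 = 608 | 30,400 | 72–78% |
| Per survey round | 7600 × 0.4/4 = 760 | 38,000 | 81–86% |

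The normal approximation is optimistic with four clusters. A t reference on 20 − (4 + 5 − 1 + 1) = 11 degrees of freedom takes the per-round figures to 73–79%.

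**The case against.** The strongest reply is that 7600 was calculated per round and the words were lost in condensing. The baseline-variance calculation lands within 3% of 7600, households are selected afresh each year, and the power then meets the stated 80%. This stands, and it rules out a stronger reading that a reader might infer: that the plan's inputs cannot give 80% power, or that the arithmetic behind 7600 is wrong. The documents support neither. Nor can it be said that only the per-round reading works. The section speaks of a change by cluster, which leaves a per-district reading open. That reading gives 72–78%, and 81–86% if 7600 already excludes non-responders, because the cell is then again 7600 × 0.5/5 = 760 children.

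A close match is still inference. A one-sided, individually randomised calculation with 20% added gives about 7,526, also close to 7600 and as a total. It ignores the stated ICC and the stepped wedge, so it is not a valid derivation, but it shows that closeness alone does not settle the unit.

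A second reply is that an article may leave rounds and formulas to the full protocol. For omitted detail that is fair. Here the article prints a size and a power that agree only after multiplying by four or five, and it supplies neither multiplier.

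A third reply is that the primary analysis is a Cox model on all reported births with right censoring, not a binary risk per child. That is correct. The figures here test the power statement on its own inputs and are not a forecast of that analysis.

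**Conclusion.** The point holds as an undefined unit on which the stated power depends. As the sentence stands, with 7600 for the study, the power is about 26–30% (30–35% with facilities as clusters), and below 70% even without clustering. Per round, the claim is approximately met; per district over all rounds, nearly so.

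The article does not show that the trial is underpowered, because it does not show which reading is meant. The figures rest on the assumptions listed in the working. The constant cluster effect matters most for the favourable reading: with a cluster autocorrelation of 0.8, the per-round power for four districts falls to 58–65%. The per-round reading also implies sampling 38,000 women, one per household, over five rounds in a population of 181,111, so the choice of reading is material to the field plan as well.

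**What to change.** Correct the sentence in the sample size section so that it gives:
- the unit of 7600 (total, per round or per district), and whether it is before or after non-response;
- the total number of women over the five rounds, for example 7,600 per round and 38,000 in all if that is what was meant;
- the stepped-wedge formula, the sidedness of the test, and the level at which the ICC of 0.005 applies;
- the resulting power, preferably with a small-sample reference given four clusters.

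If 7600 is the study total, replace the 80% by about 26–30% for four districts, or restate the detectable reduction as about 55%.

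The cost is one rewritten sentence. The correction calls for no added participants or change of design; under the total reading, the reported power becomes less favourable.

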#### Randomization

The cluster order for implementation at each step will be determined randomly by an external technical advisor using a random number generator. Randomization will occur each year 8 months prior to the rollout of the intervention in the next cluster. This will enable blinding to the random order of clusters for IH and MoH staff 7involved in implementation while also allowing for an annual 8-month planning stage prior to start of the intervention. Each cluster represents a district, with a total of 21 preselected health facilities across each of the four districts.

### Data collection and analysis

All metrics will be organized using a modified RE-AIM (reach, effectiveness, adoption, implementation, maintenance) framework [56]. Table 4 summarizes data collection and analysis plans organized by primary aim and adapted RE-AIM domains.

**Table 4 Tab4:** Summary of key study measures organized by aim and domain using modified RE-AIM evaluation framework

Study aim	RE-AIM framework domain	Outcome(s)/indicator(s)	Data source	Indicator definition/clarification
Study aim I: implementation strategy	Reach	*Health service coverage*		
		CHW home visits	Community-based household survey	Proportion of participants in the last year reporting a home visit by an IH CHW.
		CHW home treatment	Community-based household survey	Proportion of participants in the last year reporting treatment at home by an IH CHW
		Health facility treatment	Community-based household survey	Proportion of participants in the last year reporting care at a health facility.
		*Early service access for child health*		
		Malaria coverage	Community-based household survey	Proportion of children under five reported febrile receiving guideline-based treatment within 24 h of symptom onset.
		Pneumonia coverage	Community-based household survey	Proportion of children under five with a cough and proportion of those receiving guideline-based treatment within 24 h of symptom onset.
		Gastrointestinal illness coverage	Community-based household survey	Proportion of children under five with diarrhea receiving guideline-based treatment within 24 h of symptom onset.
		Malnutrition coverage	Community-based household survey	Proportion of children under five with malnutrition receiving effective treatment.
		Coverage estimate of prenatal care	Community-based household survey	Proportion of pregnant women in the last two years who completed four ANC visits.
		Percentage of births at healthcare facility	Community-based household survey	Proportion of pregnant women in the last two years who delivered in a health facility
		Percentage of births at home	*Community-based household survey*	Proportion of pregnant women who delivered at home in last 2 years.
		Coverage estimate of post-natal care	Community-based household survey	Proportion of post-partum women who received post-natal care in last 2 years.
Study aim 2: effectiveness	Effectiveness	*Primary outcome*		
		Children under five mortality rate	Community-based household survey	Using a standard birth/death history table, calculate under-five mortality rates, and compare risk of death before age five across surveys with the Cox proportional hazards regression using survey year as the explanatory variable. Children still alive and under age five at the time of survey will be right censored.
		*Secondary outcomes*		
		Neonatal mortality rate	Community-based household survey	The neonatal mortality rates from all births reported by respondents in the 5 years prior to the survey using the same methods described for under-five mortality, adjusted for 28 days.
		Children under one mortality rate	Community-based household survey	The under-one mortality rates from all births reported by respondents in the 5 years prior to the survey using the same methods described for under-five, adjusted for 1 year.
		Children under two mortality rate	Community-based household survey	The under-two mortality rates from all births reported by respondents in the 5 years prior to the survey using the same methods described for under-five, adjusted for 2 years.
		Maternal mortality rate	Community-based household survey	Exploratory maternal mortality analysis based on the sisterhood reports [57, 58].
		Quality of care parameters		
		Timeliness/promptitude of child care for malaria	Routine programmatic data	Proportion of children under five reported febrile and the proportion who received effective antimalarial treatment within 24 h of symptom onset.
		Timeliness/promptitude of child care for pneumonia	Routine programmatic data	Proportion of children under five reported with cough and the proportion of those children who received an effective pneumonia treatment within 24 h of symptom onset.
		Timeliness/promptitude of child care for diarrhea	Routine programmatic data	Proportion of children under five reported with diarrhea and the proportion of those children who received an effective treatment for diarrheal disease within 24 h of symptom onset.
		CHW technical competence	Routine programmatic data	Proportion of IH CHWs who adhere to evidence-based protocols for iCCM and maternal health.
		Facility clinical staff technical competence	Routine programmatic data	Proportion of facility clinical staff who adhere to evidence-based protocols for iCCM and maternal health.
		Equitable	Community-based household survey	Access differences in child mortality between maternal wealth quintiles, distance to facility, and education level.
		Healthcare readiness score	Health facility assessments	Examine facility changes in procurement, physical infrastructure, and management through annual readiness score [41].
Study aim I : implementation strategy	Adoption	*Community-level engagement*		
		Community engagement sessions	Routine programmatic data	Number of community forums and community members in attendance.
		*Participant-level behavior change*		
		Child care cascades for fever, pneumonia, and diarrhea	Community-based household survey	Changes in childcare-seeking behavior over time for fever, pneumonia, and diarrhea in patients presenting to health clinic, CHW, or non-clinical site. Test if these proportions increased using the same approach to mixed-effects generalized linear models as described in the primary effectiveness outcome measure.
		Women of reproductive age cascade for antenatal care, facility-based delivery, and post-natal care	Community-based household survey	Changes in pregnant women care-seeking behavior over time, services delivered by IH CHWs, facility-based delivery, as well as antenatal care and post-natal care attendance. Test if these proportions increased using the same approach to mixed effects generalized linear models as described in the primary effectiveness outcome measure.
Study aim I : implementation strategy	Implementation	*Qualitative interviews*		
		Fidelity	Key informant interviews	Degree that intervention(s) were implemented as planned in original protocol.
		Feasibility	Key informant interviews	Extent that an intervention can be carried out in a particular setting.
		Outer context [59]	Key informant interviews	Macro-level external factors including social, funding, and leadership.
		Inner context [59]	Key informant interviews	Micro-level internal factors including IH/MoH partnership, distinct issues about IH and MoH roles, feedback, facility, community, household, and individual level.
Study aim I : implementation strategy	Maintenance	*Costing and return-on-investment assessment*		
		Annual price per capita	Costing surveys	Price per capita compared to current MoH funding using the Community Health Planning and Costing Tool [48] at the cluster level.
		Return on investment	Costing surveys	Return on investment using the Community Health Planning and Costing Tool [48] and the Lives Saved Tool [49] with primary outcome at the cluster level.

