Following this successful preliminary pilot phase and considering the need, IH was requested by the MoH to expand the ICBHSS model to additional sites starting in 2018. In collaboration with the MoH and technical partners, IH is replicating the ICBHSS model in 21 distinct rural health facilities in four additional districts. In collaboration with MoH partners, IH’s ICBHSS program team designed an implementation strategy for this expansion to enhance adoption, implementation, and sustainability of the model [34–36]. This strategy enables a rollout to a new district every 12 months, and is based on pilot experience, local contextual factors as well as budgetary and feasibility considerations. As part of this expansion launched in 2018, IH and MoH partners designed a stepped-wedge randomized trial to enable a rigorous assessment of intervention effectiveness and implementation strategies to inform national policy.

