#### Primary aim 2: implementation strategy

##### Reach

We define *reach* metrics as the proportion of target population that gained access to the ICBHSS initiative services using the annual community household surveys. We will assess the implementation strategy through individual-level ICBHSS participation with community-level (vis-à-vis CHWs) and facility-level health service utilization using health service coverage estimates and early service access for child health. We will use a mixed-effects generalized linear model to compare pre-intervention to post-intervention proportions for each *reach* metric while adjusting for clustering at the facility and district level and time and allowing for district-level estimates to be random effects. Our primary analysis will not include adjustment for individual-level characteristics, as each district will serve as its own control.

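### Four maternal reach indicators look back two years while districts cross over every 12 months; if exposure follows the survey, about half the births in each first post-rollout survey precede rollout

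*Protocol article*

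**What the plan says.** **Windows.** Table 4 (Data collection and analysis) lists four maternal indicators under Reach, all over two years:
- antenatal care: "Proportion of pregnant women in the last two years who completed four ANC visits"
- facility birth: "Proportion of pregnant women in the last two years who delivered in a health facility"
- home birth: "Proportion of pregnant women who delivered at home in last 2 years"
- post-natal care: "Proportion of post-partum women who received post-natal care in last 2 years"

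The community health worker contact rows of the same table use one year, for example "Proportion of participants in the last year reporting a home visit by an IH CHW".

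**Timing.** The section on context and the ICBHSS model says: "This strategy enables a rollout to a new district every 12 months". The stepped-wedge section says: "The ICBHSS cluster initiation order will be randomized annually with four steps". It schedules household surveys in every district at baseline and at 12, 24, 36 and 48 months.

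**Analysis.** The Reach section under Primary aim 2 will "compare pre-intervention to post-intervention proportions for each" reach metric in a mixed-effects generalized linear model. The model adjusts for time and for clustering by facility and district, and each district acts as its own control. The article describes no transition period and no rule that assigns a pregnancy or birth to pre- or post-intervention by its date.

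**The concern.** The look-back is twice the step length. A survey one year after rollout therefore collects births from the year before rollout as well as the year after. If all of them take the status of the survey, the post-intervention proportion mixes unexposed and exposed births, and the estimated effect is pulled towards zero. The one-year contact indicators fit the step, so the mismatch is confined to the maternal rows.

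Four-visit antenatal care is hit harder, because a woman who delivers soon after rollout had most of her antenatal period before it.

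These are not the primary outcome, which is under-five mortality. They do measure whether the programme reaches pregnant women, which is part of the second primary aim and is meant to inform national policy. A diluted estimate could make a programme that changed place of delivery look weak. Part of any rise between the first and second post-rollout surveys would also reflect the look-back and could be taken for gradual uptake.

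**Working it through.** The article gives no figure for this point, so there is none to reproduce.

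**Inputs from the article:** look-back 24 months (Table 4); step 12 months; four districts; surveys at 0, 12, 24, 36 and 48 months.

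**Assumptions:** the first post-rollout survey falls t = 12 months after rollout (Table 2, the timeline, is not shown, so 6 to 18 months is also tested); births are spread evenly over the window; gestation lasts 9 months; exposure is coded by survey.

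**1. Births before rollout.** Share = (24 − t)/24.
- t = 12: 12/24 = 50%
- t = 6: 18/24 = 75%
- t = 18: 6/24 = 25%
- t = 24: 0%

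**2. Pregnancies wholly after rollout.** Share = (t − 9)/24.
- t = 12: 3/24 = 12.5%, so 87.5% have some time before rollout
- t = 24: 15/24 = 62.5%, so 37.5% still began before rollout

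**3. Surveys affected.** With first post-rollout surveys at 12, 24, 36 and 48 months, the districts contribute 4 + 3 + 2 + 1 = 10 post-rollout district-surveys. Four of the ten are first post-rollout surveys. The last district has no other.

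**4. Effect on the estimate.** Take the 4 × 5 layout with district effects, survey effects and one exposure indicator, on the linear scale. Each exposed cell's weight is its residual, 1 − (district mean exposure) − (survey mean exposure) + 0.5, divided by the sum of these residuals over exposed cells.

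| Survey after rollout | Residuals | Sum | Weight (sum/1.5) |
|---|---|---|---|
| First | 0.45, 0.40, 0.35, 0.30 | 1.50 | 1.0 |
| Second | 0.20, 0.15, 0.10 | 0.45 | 0.3 |
| Third | −0.05, −0.10 | −0.15 | −0.1 |
| Fourth | −0.30 | −0.30 | −0.2 |

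The residuals sum to 1.50 + 0.45 − 0.15 − 0.30 = 1.5. The weights on the later surveys cancel (0.3 − 0.1 − 0.2 = 0), so the first post-rollout surveys carry the estimate.

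For place of birth, with exposed shares 0.5, 1, 1, 1:
- t = 12: 0.5 + 0.3 − 0.1 − 0.2 = 0.50, so a true 20 points reads as **10**
- t = 6 (shares 0.25, 0.75, 1, 1): 0.25 + 0.225 − 0.3 = 0.175, so 3.5 points
- t = 18 (shares 0.75, 1, 1, 1): 0.75 + 0.3 − 0.3 = 0.75, so 15 points

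With survey effects only, the first post-rollout surveys carry 1.5/2.5 = 0.6 of the weight. The result is 0.6 × 0.5 + 0.4 × 1 = 0.70, or 14 points. The planned model has random district effects and should lie between 10 and 14, nearer 10 when districts differ clearly.

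A plain average of the ten post-rollout cells gives (4 × 0.5 + 6 × 1)/10 = 0.80, or 16 points. That average ignores time, so it does not describe the planned analysis.

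**5. Four-visit antenatal care.** As an illustration, suppose a pregnancy benefits in proportion to the part of gestation after rollout. The exposed shares are then (12 − 4.5)/24 = 0.3125 and (24 − 4.5)/24 = 0.8125, then 1. The fit gives 0.3125 + 0.3 × 0.8125 − 0.3 = 0.256, or about 5 of a true 20 points.

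**The case against.** The strongest objection is that the article never says every pregnancy takes the status of its survey. A comparison of pre- with post-intervention proportions is compatible with classing each birth by date. The survey takes a birth history, and an analysis plan that is not shown may contain the rule. This stands as a limit: a reader might infer that the plan states survey-level coding, and it does not. But the article does fix the window and the comparison, and on their natural reading the two give a diluted effect.

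Four further inferences go beyond the documents.
- **Half is not a stated figure.** It needs a survey about 12 months after rollout and even births. Any interval below 24 months still puts some pre-rollout births into the first post-rollout survey.
- **Adoption.** The maternal care cascade in Table 4 covers the same services, from the same survey and with the same type of model, but its row states no look-back. The problem there is inferred only.
- **A rise after rollout as pure artefact.** This would require an immediate full effect. A community health worker programme may build up gradually, so only part of such a rise can be put down to the look-back.
- **A one-year window as a complete repair.** With a survey 12 months after rollout, 9/12 = 75% of those pregnancies still began before it, so four-visit antenatal care is not repaired.

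**Conclusion.** The point holds for the four maternal reach indicators, conditional on survey-level exposure. With a first post-rollout survey 12 months after rollout and even births, half of its births precede rollout, and about one pregnancy in eight lies wholly after it. The estimated effect on place of birth is then about half the true one when district and survey effects are fitted. The bias is towards no effect, and the last district contributes no post-rollout survey free of it. The fitted figure is a linear approximation to the planned mixed model. The primary mortality outcome lies outside this point. The change should be made, since it needs no new design and no added sample.

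**What to change.** Keep the two-year question and state the exposure rule.
- **Place of birth and post-natal care:** assign each birth to pre- or post-intervention by its delivery date relative to the district's rollout date. The time term should then also follow delivery date. Under the assumptions above, this removes the misclassification of births.
- **Four-visit antenatal care:** count as exposed only pregnancies begun after rollout, and treat those straddling rollout as a separate transition group. Where the start of pregnancy is not recorded, it can be approximated as delivery date minus nine months.
- **Maternal adoption cascade:** state its look-back and, if it exceeds 12 months, apply the same rules.

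The cost is extra date coding, largely from the birth history already collected, and fewer fully exposed pregnancies for antenatal care. The loss is greatest in the last district, where only about 12.5% of pregnancies in its single post-rollout survey would qualify.

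Restricting to deliveries in the 12 months before each survey is an alternative for place of birth and post-natal care only. It loses about half the births per survey (12/24).
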